
### Treatment methods

SGN-35 is intravenously administered on Day 1 of each cycle (21 days/cycle). After Cycle 2, SGN-35 should be administered − 1 to + 3 days from the established day of administration, excluding cases in which a specific duration is required to achieve recovery from toxicity, appearing from the preceding cycle of SGN-35 therapy, of which the association with the investigational drug cannot be ruled out.

The drip infusion time of SGN-35 is ≥30 min. Rapid intravenous injection or bolus administration should be avoided. SGN-35 should be administered using a special line for drip infusion. It must not be mixed with other drugs. When administering SGN-35, the line for drip infusion should be washed in physiological saline (Japan Pharmacopeia) before and after SGN-35 administration so that this drug may not be mixed with other drugs.

The dose of SGN-35 is calculated based on the body weight at the baseline, and expressed as an integral number by rounding the first decimal place. In subjects with a ≥ 10% change in the body weight during the study period, it should be regulated. In subjects weighing ≥100 kg, it should be calculated, regarding the body weight as 100 kg.

In this clinical study, 1.8 mg/kg of SGN-35 is administered to 6 children as Cohort 1. Based on the incidence of DLT during the DLT evaluation period, the tolerance of the dose/administration method is evaluated. If DLT is observed in ≤1 of the 6 children, 1.8 mg/kg of SGN-35 should be regarded as tolerable. On the other hand, if DLT is observed in 2 of the 6 children, a shift to Cohort 2 may be promoted. In Cohort 2, 3 subjects are added, and 1.8 mg/kg of SGN-35 is administered. If there is no DLT in the 3 subjects, 1.8 mg/kg of SGN-35 should be regarded as tolerable. However, if the third episode of DLT appears in Cohort 2, no patient will be newly registered.

### Dose-limiting toxicity (DLT)

DLT should be evaluated from the initial administration of this drug until administration on the first day of administration in Cycle 2. In subjects in whom the appearance of toxicity made this-drug administration in Cycle 2 impossible, and treatment was discontinued, DLT must be evaluated until safety follow-up.

Among adverse events of which the association with this drug cannot be ruled out, those corresponding to the following items are regarded as DLT. The grade is evaluated according to “Common Terminology Criteria for Adverse Events v4.03”:Grade 4 neutropenia persisting for ≥8 daysGrade 3 febrile neutropenia requiring the administration of antibioticsGrade 4 febrile neutropeniaGrade 4 thrombocytopenia

Grade 3 ≤ non-hematological toxicity. However, the followings are excluded:Grade 3 fatigueGrade 3 or 4 nausea (supportive therapy is permissible)Grade 3 or 4 vomiting (supportive therapy is permissible)Grade 3 abnormalities in non-hematological laboratory data showing recovery to grade 1 or a baseline condition (cases in which there were abnormalities at study enrollment) within 14 daysGrade 3 or 4 allergic reactions

DLT will be finally evaluated by the trial-coordinating investigator.

### Follow-up

In subjects treated with this drug, the following assessments should be performed 28 days (7 days) after the final administration if it does not exceed the data cut-off day. These assessments should be conducted before the start of posttreatment. If examinations/observation/surveys are impossible for unavoidable reasons, such as complete withdrawal from this study, drop-out, death, and unfavorable conditions, the reasons must be recorded in original materials, and this study should be completed. In this case, deficits in examination/observation/survey items scheduled 28 days after the final administration are not regarded as deviations from the study protocol.

### Efficacy assessment method

The anti-tumor effects of SGN-35 are evaluated only in patients with measurable lesions according to the Revised Response Criteria for Malignant Lymphoma [13] based on the results of cervical, thoracic, abdominal, and pelvic computed tomography (CT) and positron emission tomography (PET), which were performed at the points established in the study protocol. At each point, the treatment response is assessed as CR, PR, SD, or PD. Lesions meeting the following criteria are regarded as measurable:Nodular masses of lymph nodes or extranodular organs evaluated as lymphoma on CTThe lesion can be clearly measured in two intersecting directions on cross sections of CT.The maximum diameter exceeds 1.5 cm on cross sections of CT.Positive findings on FDG-PET.

Among measurable lesions, 6 lesions at maximum in the order of maximum diameter on cross sections of CT should be selected as target lesions regardless of nodular or extranodular lesions.

If subjects are positive for bone marrow infiltration on baseline assessment, follow-up by bone marrow aspiration or biopsy may be necessary. To evaluate the treatment response as CR, subjects must be negative for bone marrow infiltration. If morphological examination-based evaluation is impossible, the results of examination using immunostaining should also be considered.

### Statistical analysis

#### Analysis set

Patients enrolled in this study and treated with the investigational drug at least one session are regarded as a full analysis set (FAS). However, patients who were shown to violate the study protocol or GCP after enrollment and those who were considered ineligible after enrollment should be excluded from FAS. Safety analysis set is defined as patients enrolled in this study and treated with the investigational drug at least one session. DLT analysis set is defined as the following subjects:Subjects with ≥1 DLT during the DLT assessment period (from initial administration until administration in Cycle 2)orThose to whom an established dose of SGN-35 was administered in Cycle 1, and in whom observation for DLT assessment was completed.

Pharmacokinetics (PK) analysis set is defined as patients enrolled in this study and observed at least one PK data.

### Safety endpoints

The incidence of DLT will be calculated in DLT analysis set. The incidence of adverse events/reactions to the investigational drug will be calculated with respect to events, severity, and grade with safety analysis set.

### Efficacy endpoints

The ORR, CR rate, and their 95% confidence interval will be calculated in the FAS. To estimate the response duration, PFS, and EFS, the Kaplan-Meier method will be used. Their 95% confidence interval will be calculated with Greenwood’s formula.

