**Methods:**

Phase I clinical study of SGN-35 involving children with recurrent or refractory CD30-positive Hodgkin’s lymphoma or systemic anaplastic large cell lymphoma (BV-HLALCL study) is being conducted for pediatric patients in order to evaluate the safety, feasibility and preliminary clinical effectiveness of brentuximab vedotin. SGN-35 is intravenously administered on Day 1 of each cycle (21 days/cycle). The dose of SGN-35 is calculated based on the body weight at the baseline. The primary endpoint is dose limiting toxicity and incidence of adverse events. The secondary endpoints are pharmacokinetics, response rate, complete remission rate, response duration, progression-free survival and event-free survival. The reduction rate of tumor will be calculated according to revised response criteria for malignant lymphoma for measurable tumor. Six pediatric patients will be enrolled in this study.

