## Background

Hodgkin’s lymphoma (HL) and anaplastic large-cell lymphoma (ALCL) are the two most common tumors expressing CD30. The treatment of HL and ALCL has largely relied on cytotoxic chemotherapy.

Basic treatment for childhood HL consists of chemotherapy and low-dose involved field radiotherapy (LD-IFRT). Chemotherapy alone or a combination of chemotherapy and LD-IFRT is selected in accordance with individual children. Furthermore, the intensity of initial chemotherapy is determined based on early treatment responsiveness in order to avoid unnecessary additional chemotherapy or radiotherapy. Chemotherapeutic regimens and treatment schedules differ among clinical studies. In Japan, treatment has not been standardized, and is selected based on the results of international clinical studies in accordance with individual patients. In a representative clinical study regarding childhood HL, the GPOH-HD-2002 study, chemotherapy with vincristine, etoposide, prednisolone, doxorubicin, cyclophosphamide, and procarbazine and LD-IFRT for some patients improved the 5-year event-free survival rate to 89%, and the 5-year survival rate to 97% [1]. In Japan, this treatment is selected for many patients. Treatment for patients with treatment resistance/relapse, accounting for approximately 10% of those with childhood HL, has not been standardized. Patients with local relapse after initial treatment for a low-risk group may be saved by chemotherapy and LD-IFRT, but the exacerbation-free survival rate ranges from 30 to 65% in other patients with treatment resistance/relapse even when hematopoietic cell transplantation is performed [2, 3].

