#### End points

<Primary endpoints>(i)DLT(ii)Adverse events

<Secondary endpoints>(i)Pharmacokinetics (serum concentration of SGN-35, plasma concentration of MMAE, and serum concentrations of all antibodies)(ii)Overall response rate (ORR)

ORR refers to the proportion of subjects with complete remission (CR) or partial remission (PR) as the best comprehensive response in analysis set.(iii)Complete remission rate

CR rate refers to the proportion of subjects with CR as the best comprehensive response in analysis set.(iv)Response duration

The response duration refers to a duration from the first day of CR or PR evaluation until the first day of progressive disease (PD) evaluation or the day of death related to some factor (earlier). With respect to data on the response duration in subjects continuing to participate in this study until analysis without PD, those receiving anti-tumor treatment other than the test regimen and stem cell transplantation, and those excluded from this study before CR or PR achievement, the final day of image assessment on which disease progression is ruled out in lesions to be measured is regarded as the day of censoring.(v)Progression-free survival (PFS)

PFS refers to a period from the first day of administration until the first day of PD evaluation or the day of death related to some factor (earlier). With respect to data on PFS in subjects who continued study participation until analysis without showing PD, those who received anti-tumor treatment other than test treatment and stem cell transplantation, and those excluded from this study before CR or PR evaluation, the last day of image assessment on which disease progression was ruled out in lesions to be measured is regarded as the day of censoring. Subjects in whom image assessment after initial administration was not conducted, is censored at day 1.(vi)Event-free survival (EFS)

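### With six patients (nine at most), the Greenwood intervals fixed for response duration, PFS and EFS cannot be relied on for 95% coverage and give no usable interval before the first event.

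*Protocol article*

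**What the plan says.** The Efficacy endpoints section of the protocol article sets the estimator, "To estimate the response duration, PFS, and EFS, the Kaplan-Meier method will be used", and then the interval: "Their 95% confidence interval will be calculated with Greenwood’s formula". It mentions no transformation and no rule for a curve on which no event has occurred.

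The numbers behind these curves are small:

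- The abstract plans six: "Six pediatric patients will be enrolled in this study".
- Treatment methods allows one extension: "In Cohort 2, 3 subjects are added, and 1.8 mg/kg of SGN-35 is administered". The maximum is therefore 6 + 3 = 9.
- The full analysis set can be smaller than the number treated, because "those who were considered ineligible after enrollment should be excluded from FAS".
- Response duration starts at a response ("The response duration refers to a duration from the first day of CR or PR evaluation"), so only responders contribute to it.

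All three endpoints are secondary (abstract and End points). The primary endpoints are dose-limiting toxicity and adverse events.

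**The concern.** Greenwood's formula estimates the variance of a Kaplan-Meier estimate. An interval built on it relies on approximate normality, which needs far more than six to nine patients. The variance is also computed from the observed events, so it shrinks as the observed survival approaches 100% and is zero when nobody has had an event. The interval is then narrowest, or absent, when the results look best.

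The study has one arm and no comparator, so these intervals are the main statement of uncertainty for time-to-event efficacy. The Discussion expects the study to establish efficacy as well as safety in Japanese children. An interval that is too narrow, or collapsed at 100%, would make six patients look more informative than they are.

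**Working it through.** **Inputs.** n = 6, or 9 with Cohort 2, and the nominal level of 95%, are from the article. The true survival S at a given time is an assumption, so a range is shown. The only survival range that the article gives for relapsed or refractory childhood Hodgkin's lymphoma is in Background: "the exacerbation-free survival rate ranges from 30 to 65% in other patients with treatment resistance/relapse". It serves here as one plausible range for S and is not a forecast for this drug.

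**The plan's own figure.** The only figure to reproduce is the nominal 95%; the sample size of six comes with no precision calculation.

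**Step 1: the variance.** Greenwood: Var = Ŝ² × Σ d/[r(r − d)], with d events among r at risk. If nobody is censored before the time point, Ŝ = x/n and this reduces to Ŝ(1 − Ŝ)/n. Check for 5/6: (25/36) × 1/(6 × 5) = 0.0231, and (5/6)(1/6)/6 = 0.0231.

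**Step 2: plain intervals, Ŝ ± 1.96 × SE, n = 6.**

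| Event-free | Interval |
|---|---|
| 0/6 | 0% to 0% |
| 1/6 | −13.2% to 46.5% |
| 2/6 | −4.4% to 71.1% |
| 3/6 | 10.0% to 90.0% |
| 4/6 | 28.9% to 104.4% |
| 5/6 | 53.5% to 113.2% |
| 6/6 | 100% to 100% |

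**Step 3: coverage.** Add the Binomial(6, S) probabilities of the counts whose interval contains S. At S = 0.5 these are 2, 3 and 4 event-free: (15 + 20 + 15)/64 = 78.1%. At S = 0.8 they are 3, 4 and 5: 0.082 + 0.246 + 0.393 = 72.1%. The chance of no event is S⁶.

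| True S | Coverage, plain scale | Chance of no event |
|---|---|---|
| 0.3 | 87.1% | 0.1% |
| 0.4 | 91.2% | 0.4% |
| 0.5 | 78.1% | 1.6% |
| 0.6 | 91.2% | 4.7% |
| 0.65 | 90.2% | 7.5% |
| 0.7 | 87.1% | 11.8% |
| 0.8 | 72.1% | 26.2% |
| 0.9 | 46.7% | 53.1% |

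Over S from 0.01 to 0.99 coverage never exceeds 91.2%. It averages 87.9% over 0.30 to 0.65 and 81.9% over 0.3 to 0.9.

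**Step 4: other sample sizes and censoring.** With nine patients, plain coverage averages 86.5% over S of 0.3 to 0.9, peaks at 93.5% and is 60% at 0.9. The chance of no event is then 0.8⁹ = 13.4% at 0.8 and 0.9⁹ = 38.7% at 0.9. With four responders coverage is at most 87.5%. In simulations with six patients and an assumed 40% chance of censoring by the time point, it was 80.6% at S = 0.5, 81.3% at 0.65 and 62.7% at 0.8.

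**Step 5: log-log scale, n = 6.** The limits stay inside 0% to 100% (5/6 gives 27.3% to 97.5%). Coverage is 96.9% at S = 0.5 and averages 92.9% over 0.30 to 0.65. With no event the variance is still zero and the interval is undefined. Counting those samples as misses, coverage is 72% at 0.8 and 45% at 0.9.

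**Step 6: exact comparison, n = 6, no censoring.** For 6/6 the lower Clopper-Pearson limit is 0.025^(1/6) = 0.541, so the interval is 54.1% to 100%. For 5/6 it is 35.9% to 99.6%. Coverage is 96.6% to 99.8% over S of 0.3 to 0.9.

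**The case against.** **The scale is not stated.** Greenwood's formula is a variance and can be used on the plain, log or log-log scale. A condensed article may leave the scale to the SAP. This stands: a reader might infer that the plan commits itself to limits above 100%, but the text does not say so. The overshoot and the shortfall at S = 0.5 belong to the plain reading only. The zero variance before the first event does not depend on scale, so no SAP detail that keeps Greenwood removes it.

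**A missing interval is visible.** On the log-log scale the no-event case shows as no interval, and counting it as a miss mixes two problems. At S = 0.8, among samples with at least one event, coverage is 0.721/(1 − 0.262), about 98%. This is fair for the log-log scale. On the plain scale the same case would be printed as 100% to 100%, and on either scale the reader loses the lower limit of 54% that six event-free patients support.

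**High survival is assumed.** The worst figures need S of 0.8 to 0.9, while the article cites 30% to 65%. At 0.65 the chance of no event is 7.5%. A reader might infer that no event is the most likely early result. The documents fix no time point that would support this, and with six patients it is the most likely count only when S exceeds 6/7, about 86%.

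**The endpoints are secondary.** This stands. The tolerability rule uses only counts of dose-limiting toxicity, and no efficacy interim is planned.

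**Conclusion.** The concern holds in a limited form. A large-sample variance is prescribed for curves on six patients, nine at most. On the plain scale with n = 6 and no censoring, the nominal 95% is not reached at any true survival. The shortfall is about 4 to 8 points at 0.3 to 0.4 and 0.6 to 0.7, 17 points at 0.5, and 23 to 48 points at 0.8 to 0.9. On the log-log scale the middle range is close to nominal. The failure common to all scales is that there is no usable interval before the first event.

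The sizes rest on the assumed values of S and, outside the simulations, on no censoring before the time point. The consequence is confined to the reported precision of secondary efficacy results.

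Three wider readings are not supported:

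- That response duration must rest on fewer than six patients. All six could respond, and up to nine could be treated.
- That the intervals for overall response and complete remission rates are also wrong. The section does not tie them to Greenwood.
- That a regulatory decision hangs on these intervals. The article states an aim to expand the indication and gives these intervals no role in it.

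**What to change.** In Efficacy endpoints, and in the SAP if it repeats the sentence, replace the Greenwood interval for response duration, PFS and EFS with a small-sample exact-type interval for the Kaplan-Meier estimate. The beta product confidence procedure is suitable: it allows for censoring, reduces to Clopper-Pearson without it, and gives an interval when no event has occurred (54% to 100% for 6/6, 36% to 99.6% for 5/6). No change to the response-rate intervals is asked for.

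The cost is one sentence and wider, somewhat conservative intervals. Sample size, conduct and treatment are untouched. If Greenwood is kept for convention, the plan should at least name the scale and say what is reported before the first event; that is a weaker repair.

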### Interim analysis and monitoring

As it may be difficult to obtain sufficient information useful for efficacy assessment during this clinical study, interim analysis for efficacy assessment will not be conducted.

To confirm that this clinical study is being safely and adequately conducted according to the study protocol and relevant regulations, and that data reliability is sufficiently secured, hospital visit monitoring with direct reading, including the comparison of case reports with original materials by the monitoring director or persons in charge of monitoring, will be performed. The principle investigator/investigators must accept hospital visit monitoring by the monitoring director and persons in charge of monitoring designated before the start of this study, and provide all study-associated records, such as original materials, for direct reading.

When there is an inconsistency between original materials and case reports, the monitoring director or persons in charge of monitoring must obtain records explaining its reasons from the chief investigator.

### Pharmacokinetics

In a PK analysis set, pharmacokinetic parameters (Cmax, AUC, etc) for serum concentration of the drug will be estimated using non-compartmental analysis. Similarly, the serum concentration of all antibodies and plasma concentration of MMAE will be analyzed. Blood specimens used for evaluation of pharmacokinetics are collected at the time shown in Table 1.

**Table 1 Tab1:** Timing of sample collection for pharmacokinetics assessment

Cycle	Date	Time	Permissible range
Cycle 1	Day 1	Before administration	≤ 2 h.
		10 min after the completion of administration	± 5 min.
	Day 2	24 h after the completion of administration	± 1 h.
	Day 4	72 h after the start of administration	± 2 h.
	Day 8	168 h after the start of administration	± 3 h.
	Day 15	336 h after the start of administration	± 3 h.
Cycle 2	Day 1	Before administration	≤ 2 h.
		10 min after the completion of administration	± 5 min.
	Day 2	24 h after the completion of administration	± 2 h.
	Day 4	72 h after the start of administration	± 2 h.
	Day 8	168 h after the start of administration	± 3 h.
	Day 15	336 h after the start of administration	± 3 h.
Cycle 3	Day 1		≤ 2 h.
–	Safety follow-up		

Blood samples for pharmacokinetics assessment should be collected at the following points. In subjects in whom blood collection is considered difficult, blood samples may be collected before administration in each cycle

## Discussion

Pediatric patients should be administered medicines that have been appropriately evaluated for their use. In the past, however, new approved drugs have been used for pediatric patients without assessment of the efficacy and safety in those patients. Clinical studies involving adults with recurrent or refractory HL or ALCL in Japan and other countries demonstrated the efficacy and safety of SGN-35 [10, 11]. The present study will prove the efficacy and safety of SGN-35 in Japanese children.

## Abbreviations

ADC: Antibody-drug conjugate
ALCL: Anaplastic large-cell lymphoma
ALT: Alanine aminotransferase
AST: Aspartate aminotransferase
CR: Complete remission
CT: Computed tomography
DLT: Dose-limiting toxicity
EFS: Event-free survival
FAS: Full analysis set
G-CSF: Granulocyte-colony stimulating factor
HBs: Hepatitis B virus surface
HL: Hodgkin’s lymphoma
LD-IFRT: Low-dose involved field radiotherapy
MMAE: Monomethylauristatin E
MTD: Maximum tolerance dose
NYHA: New York Heart Association
ORR: Overall response rate
PD: Progressive disease
PET: Positron emission tomography
PFS: Progression-free survival
PK: Pharmacokinetics
PR: Partial remission
SALCL: Systemic ALCL
SG: Inc., Seattle Genetics, Inc.
ULN: Upper limit of normal
